## Discussion

3

Total neoadjuvant treatment has gained wide recognition in recent years for the treatment of locally advanced rectal cancer due to a greater opportunity for patients to receive all required chemotherapy before surgery, to the benefit of a micrometastasis targeting approach, as well as an increase in the likelihood of achieving a complete clinical or pathologic response. It has been shown in a meta‐analysis by Kasi et al. that TNT leads to significantly higher pCR (29.9% vs. 13%) and DFS rates compared with conventional neoadjuvant chemoradiation plus surgery with or without adjuvant chemotherapy [10]. Patients who do not achieve a pCR after conventional CRT are usually given adjuvant chemotherapy while having a colostomy, and therefore, this leads to higher toxicity and lower compliance in these patients. TNT is advantageous to these patients as they will not have to endure adjuvant chemotherapy. It is proposed by multiple studies that higher pCR rates lead to better oncologic outcomes [21]. The higher rate of complete response seen with TNT presents opportunities for organ‐preserving, watch‐and‐wait strategies. It is obvious that patients who forgo TME after achieving a cCR have better urinary, bowel, and sexual function and subsequently a better quality of life [22].

TNT strategies presented thus far include either short‐course or long‐course chemoradiation with either induction or consolidation chemotherapy or both, all given before surgery.

Three randomized clinical trials have thus far compared neoadjuvant SCRT + TME versus conventional LCRT. The RAPIDO trial recruited 920 high‐risk rectal cancer patients with either cT4, cN2, extramural venous invasion, compromised mesorectal fascia, or malignant extramesorectal/lateral pelvic lymph nodes and not only showed a higher pathologic complete response rate in the neoadjuvant SCRT plus consolidation chemotherapy (28% vs. 14%, *p* < 0.0001), but also a lower cumulative incidence of disease‐related treatment failure (HR: 95% CI: 0.6–0.95, *p* value: 0.019) compared with the standard LCRT with or without adjuvant chemotherapy [13]. However, the authors also reported in their updated 5‐year results a higher rate of locoregional recurrence in the R0/R1 subset of patients who received SCRT compared with the standard chemoradiation arm (10.2% vs. 6.1%, *p* value: 0.027) as well as a higher rate of breached mesorectum in the patients with a recurrence (21% in the SCRT vs. 4% standard group, *p* value: 0.048) [23]. Some researchers have warned against using SCRT in patients with high‐risk local features, as enrolled in the RAPIDO trial, due to the observed higher LRR rates, and questioned the superiority of SCRT to LCRT in the TNT setting as the comparator arm, considering the important fact that it did not include induction/consolidation chemotherapy prior to the surgery [24].

The STELLAR trial evaluated the noninferiority of SCRT plus consolidation chemotherapy (CAPOX × 4) versus conventional LCRT followed by TME and adjuvant CAPOX (to reach 6 cycles for both groups) regarding DFS in low and middle‐rectum patients with T3‐4 and/or *N*+ stage. This study not only proved the noninferiority of DFS in the TNT group but also showed a superior 3‐year OS of 86.5% versus 75.1% compared with conventional LCRT (*p* value: 0.033) [25].

Finally, the POLISH II trial compared neoadjuvant SCRT plus consolidation chemotherapy (FOLFOX4 × 3) with conventional neoadjuvant CRT (concurrent 5FU, leucovorin, with/without oxaliplatin) in fixed cT3 and cT4 rectal cancer patients; however, despite the investigational arm not being considered a standard TNT approach, unlike the previously mentioned two similarly designed studies, the R0 resection (77% vs. 71%) and pCR (16% vs. 12%) rates were not significantly different between the two arms. Also, other than an early OS benefit of 9% in 3 years, there was no difference in DFS and OS in the 8‐year follow‐up [26].

Following these reports, a meta‐analysis was performed to evaluate short‐course RT followed by consolidation chemotherapy versus long‐course chemoradiation on seven studies including 1865 participants and showed a higher pCR rate (HR: 95% CI: 1.41–2.15, *p* < 0.01), better DFS (RR: 95% CI: 1.02–1.18, *p* value: 0.01), but similar OS and toxicity rates [27].

Few trials have addressed the efficacy of TNT using LCRT as well. In the phase 3 PRODIGE‐23 study, 461 healthy adults with cT3‐4 N0 rectal cancer were randomized to receive either six biweekly cycles of neoadjuvant FOLFIRINOX followed by LCRT and TME and adjuvant chemotherapy for 3 months (mFOLFOX6 or capecitabine) or standard LCRT followed by TME and 6 months of adjuvant chemotherapy. The 3‐year DFS was 76% in the intervention group vs. 69% in the standard group (HR: 95% CI: 0.49–0.97, *p* value: 0.034) [12]. Also, the GCR‐3 phase 2 study randomized 108 patients with T3‐4 or *N*+ middle or distal rectal cancer to receive either 4 cycles of neoadjuvant CAPEOX followed by LCRT and TME or standard LCRT followed by TME and 4 cycles of adjuvant CAPEOX. The 5‐year follow‐up results showed no significant difference in rates of local recurrence, distant metastasis, DFS, or OS between the study arms [28].

The sequence of chemotherapy regarding chemoradiation in TNT protocols has been a topic of research as well. Two trials have compared induction with consolidation chemotherapy in the TNT setting. The OPRA trial showed that in the TNT setting, T3‐4 and/or *N*+ rectal cancer patients who received consolidation chemotherapy after LCRT achieved a higher TME‐free survival compared with those receiving induction chemotherapy followed by LCRT (53% vs. 41%, *p* value: 0.01), despite similar DFS, local recurrence‐free survival, distant metastasis‐free survival, and OS [18].

The German CAO/ARO/AIO‐12 trial similarly compared induction and consolidation chemotherapy in the TNT setting for T3‐4 and/or *N*+ patients and showed a higher pCR rate in the consolidation group (25%) versus the induction group (17%), and after 43 months of follow‐up, the 3‐year DFS was 73% in both groups [29]. Unlike the OPRA trial, this study did not offer nonoperative management to the patients achieving a cCR. Based on these trials, it is presumable that consolidation chemotherapy is superior to induction chemotherapy in terms of achieving a complete response to TNT protocols. This might be due to the higher compliance of patients with the completion of the chemoradiation in consolidation schedules as compared to induction chemotherapy, as also stated by the German authors. Also, it can be hypothesized that induction chemotherapy might, by causing early lymphodepletion, result in reduced capabilities of the immune system in the identification of the cancer antigens being presented by the damaged tumor cells during chemoradiation. This could subsequently result in diminished targeting of the cancer cells by the patient's immune system. Based on these two studies, we have opted for the consolidation chemotherapy sequence.

A recent retrospective study by Romesser et al. [19] compared the results of SCRT and LCRT given as part of a TNT approach in a single institution. Both groups reached a cCR rate of 46%; however, cCR was higher in both groups if radiation was given prior to chemotherapy. The 2‐year organ preservation rate was 40% for LCRT versus 29% for SCRT, although the 2‐year OS, DFS, and distant recurrence were similar between the two groups.

No study has yet prospectively compared SCRT and LCRT, both given with TNT protocols, and this was the rationale for us to design the current study in which we will be comparing the efficacy and toxicities of both SCRT and LCRT, followed by consolidation chemotherapy to determine the best TNT strategy for rectal cancer patients. Due to the present concerns about the re‐growth rate in SCRT patients who achieve a clinical complete response in a report from the Memorial Sloan‐Kettering Cancer Center [30], and the concerning rate of local recurrence in the updated long‐term analysis of the RAPIDO trial [23] we will not be recruiting low‐lying tumors as an extra precaution measure until more convincing evidence is available regarding the noninferiority of SCRT compared with LCRT for organ preservation. A similar study is also being conducted in Germany (ACO/ARO/AIO‐18.1, NCT04246684) [15] with a primary endpoint of 3‐year organ preservation rate and an estimated completion date of 2028.

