#### Secondary Endpoints

2.4.2

Following the completion of treatment, patients will be monitored, and the rates of local, regional, and distant failure will be recorded in 3 and 5 years, respectively. Local recurrence‐free survival, regional recurrence‐free survival, distant metastasis‐free survival, and OS will be evaluated as secondary endpoints, with the last chemotherapy cycle date being the reference time point for survival outcome calculation. We will also perform a subgroup analysis on an MRI‐defined high‐risk group with either of the following features: elevated CEA (> 20 ng/mL), cT4, cN2, positive CRM, presence of EMVI, pathologic extramesorectal lymphadenopathies, and/or large (short axis diameter ≥ 1 cm) mesorectal lymph nodes. Treatment‐related adverse events, including gastrointestinal, genitourinary, hematologic, and skin toxicities, will be graded using the Common Terminology Criteria for Adverse Events (CTCAE) version 5 and compared between the two treatment arms. Throughout the study period, patients will undergo periodic blood tests and physical examinations.

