### Randomization and Allocation

2.5

The permuted block randomization method will be employed using a web‐based computer software, in which patients will be allocated into two groups (SCRT and LCRT) with random block sizes of four. Allocation will be done according to the generated numbers and the time of enrollment.

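### High-risk status is known at baseline and is the trial's own subgroup factor, but it is used neither to stratify allocation nor to adjust the arm comparison

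*Protocol article*

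**What the plan says.** **Allocation.** Section 2.5 of the protocol article uses permuted blocks: "patients will be allocated into two groups (SCRT and LCRT) with random block sizes of four". Patients are assigned from the generated list in order of enrolment. No stratification factor is named.

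**Analysis.** Section 2.9 compares qualitative data between arms with Pearson's chi-squared test in the intention-to-treat population. A binary logistic regression is planned to find predictors of cCR. It is not described as the model that estimates the treatment effect.

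**High-risk status.** Section 2.4.2 plans a subgroup analysis in a high-risk group. Its features include "cT4, cN2, positive CRM, presence of EMVI, pathologic extramesorectal lymphadenopathies", together with CEA above 20 ng/mL and large mesorectal nodes. The opening of section 2 places the MRI reading and the tumour markers in the initial work-up. Eligibility depends on the MRI stage, and a CEA above 20 ng/mL triggers a PET scan to rule out metastases, so both are available before allocation.

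**Eligibility and its rationale.** The abstract admits standard-risk and high-risk disease. Section 2.1 admits T4 and N2, and section 2.2 excludes none of the high-risk features. The Discussion explains the 5 cm limit: "we will not be recruiting low‐lying tumors as an extra precaution measure until more convincing evidence is available regarding the noninferiority of SCRT". It gives two reasons. One begins "Due to the present concerns about the re‐growth rate in SCRT patients who achieve a clinical complete response"; the other is "the concerning rate of local recurrence in the updated long‐term analysis of the RAPIDO trial".

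**The concern.** The trial singles out one binary baseline factor as important enough for its own subgroup analysis, and it collects that factor before randomisation. The stated allocation and the stated test both leave it out. Chance can then put noticeably more high-risk patients in one arm. An unadjusted comparison of cCR or local control would carry that difference, and readers would ask about it when the results appear. If the factor is prognostic, ignoring it also gives up some precision that costs nothing to obtain.

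The Discussion makes the question more visible. It describes RAPIDO as enrolling "high‐risk rectal cancer patients with either cT4, cN2, extramural venous invasion, compromised mesorectal fascia, or malignant extramesorectal/lateral pelvic lymph nodes", and it reports more locoregional recurrence in patients "who received SCRT compared with the standard chemoradiation arm (10.2% vs. 6.1%, *p* value: 0.027". It then adds: "Some researchers have warned against using SCRT in patients with high‐risk local features, as enrolled in the RAPIDO trial, due to the observed higher LRR". A factor discussed in these terms is the natural candidate for stratification.

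**Working it through.** **1. The plan's own figure.** Section 2.7 gives 76% vs 52% cCR, two-sided 5%, 90% power. The unpooled formula is n = (1.960 + 1.282)² × (0.76×0.24 + 0.52×0.48) / 0.24² = 10.51 × 0.432 / 0.0576 = 78.8, so 79 per arm. This reproduces. Section 2.7 recruits 95 per arm (190), whereas the abstract randomises 158, so both sizes are carried below.

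**2. Chance imbalance.** The high-risk share p is not given; 30%, 50% and 70% are assumed. Treating the arms as independent binomials, the SD of the difference in share is √(2p(1−p)/n). The last column simulates blocks of four (20,000 trials per setting).

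| Per arm | p | SD (points) | P(difference ≥ 10 points), exact binomial | Same, blocks of four |
|---|---|---|---|---|
| 95 | 30% | 6.65 | 13.2% | 13.5% |
| 95 | 50% | 7.25 | 16.8% | 16.9% |
| 95 | 70% | 6.65 | 13.2% | 12.8% |
| 79 | 30% | 7.29 | 19.3% | 18.4% |
| 79 | 50% | 7.96 | 23.3% | 22.8% |
| 79 | 70% | 7.29 | 19.3% | 18.4% |

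The exact chance of 15 points or more is 2.1–3.5% at 95 per arm and 4.6–6.7% at 79.

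**3. With stratified blocks.** An unfinished block of four can leave the arms at most 2 patients apart within a stratum. The difference in high-risk share is then limited to about 2/95 = 2.1 points, or 2/79 = 2.5 points.

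**4. Effect on cCR.** Shift = imbalance × prognostic gap. If high-risk status lowers cCR by 20–30 points (assumption), a 10-point imbalance shifts the arm difference by 0.10×0.20 = 2 to 0.10×0.30 = 3 points. The planned difference is 24 points, and its standard error at 79 per arm is √(0.432/79) = 7.4 points.

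**5. Effect on local control.** If local recurrence is 5–15 points higher in high-risk patients (assumption), the same imbalance shifts the arm difference by 0.5–1.5 points. With recurrence near 8% (assumption), the standard error at 95 per arm is √(2×0.08×0.92/95) = 3.9 points.

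**6. Gain from using the factor (cCR, 79 per arm, same 20–30-point gap in both arms).** Adjustment removes about g²p(1−p) from each arm's variance.
- Unadjusted: z = 0.24/√(0.432/79) = 3.25; power = Φ(3.25 − 1.96) ≈ 90%.
- p = 50%, g = 20 points: the variance sum falls by 2×0.04×0.25 = 0.020 to 0.412; z = 3.32; power ≈ 91%.
- p = 50%, g = 30 points: the variance sum falls by 2×0.09×0.25 = 0.045 to 0.387; z = 3.43; power ≈ 93%.

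The gain is about 1–3 points of power.

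**The case against.** **Unstratified allocation is valid.** Permuted 1:1 blocks balance every covariate in expectation, and the chi-squared test keeps its type I error. This stands. The shifts in steps 4 and 5 are well inside one standard error.

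**The subgroup analysis is not harmed by bias.** It compares arms within high-risk patients. Unequal shares change the subgroup arm sizes a little but do not bias that comparison. This stands too.

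**Covariate adjustment may sit in an analysis plan that is not shown.** That is possible, so its absence from the article is not itself an error. The allocation rule, however, is stated in section 2.5, and it contains no stratum.

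**A stronger reading is tempting and is not supported.** A reader might infer that the 5 cm limit misses the risk it was meant to address, because RAPIDO's recurrences are tied to features that remain eligible. The text does not bear this out:
- RAPIDO is only one of two reasons. The other, re-growth after a complete clinical response, concerns organ preservation and does not depend on RAPIDO.
- The limit also removes high-risk tumours that are low-lying, and the Background names low-lying tumours alongside high-risk ones as poorly controlled locally under conventional therapy.
- Enrolment of high-risk patients is openly stated in the abstract and anticipated in section 2.4.2.
- The warning about SCRT is reported as the view of some researchers. The 10.2% vs 6.1% is a treatment contrast in a population described as wholly high-risk, so it cannot show that high-risk status modifies the effect of SCRT.
- The high-risk definition in section 2.4.2 is broader than the RAPIDO list, since it adds CEA and large mesorectal nodes.

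Nor should a 10-point imbalance in share be set beside the 4.1-point RAPIDO excess (10.2 − 6.1). One is a difference in case mix and the other a difference in recurrence; step 5 gives the proper conversion.

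**Conclusion.** The point holds as a cheap improvement, not as a flaw that threatens the trial. A factor that is already collected, and that the trial treats as important, is left out of the stated allocation and the stated comparison. For an assumed high-risk share of 30–70%, the chance of a 10-point or larger imbalance is 13–17% with 190 patients and 18–23% with 158. The resulting shift in the cCR difference is small, about 2–3 points, and the power to be gained is about 1–3 points. Both depend on an assumed 20–30-point lower cCR in high-risk patients. If the factor is weakly prognostic, the shift and the gain shrink towards zero, and what remains is the credibility of a visibly balanced baseline table.

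The mismatch between the RAPIDO part of the rationale and the Discussion's own description of that trial is a matter of wording. It is neither a contradiction nor an eligibility error.

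**What to change.** 1. Stratify the permuted blocks by high-risk status as defined in section 2.4.2 (yes/no).
2. Use the same factor in the comparisons: a Mantel-Haenszel test with a stratified risk difference, or a logistic model containing arm and high-risk status, for cCR; and a stratified or adjusted Cox model for local control. The stratified risk difference stays on the scale of the sample-size calculation.
3. If recruitment is too advanced to change allocation (section 2.8 ends it in September 2025), prespecify the adjustment in step 2 alone, before outcome data are compared by arm. Most of the precision gain comes from the adjustment in any case.
4. As wording only, reconcile the RAPIDO reason for the height limit with the Discussion's description of that trial and with the eligibility stated in the abstract and section 2.1. Who is eligible is for the sponsor to decide.

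The cost is one binary stratum in the web-based software and one line in the analysis. The small downside is that the baseline MRI features, including the nodal short-axis diameter, and the CEA result must be entered before allocation. The work-up already provides for MRI nodal assessment and CEA.

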## Ethics Statement

The study protocol was approved by the Research Ethics Committees of Imam Khomeini Hospital Complex–Tehran University of Medical Sciences (TUMS) (approval number: IR.TUMS.IKHC.REC.1401.238).

## Consent

Informed consent will be obtained from patients after a thorough explanation of the treatment process. If a patient decides to withdraw from the study, they will be removed and receive the standard protocol treatment.

## Data Availability

The datasets used and/or analysed during the current study are available from the corresponding author on reasonable request.
